## Abstract

**Background:**

With a decline in malaria burden, innovative interventions and tools are required to reduce malaria transmission further. Mass drug administration (MDA) of artemisinin-based combination therapy (ACT) has been identified as a potential tool to further reduce malaria transmission, where coverage of vector control interventions is already high. However, the impact is limited in time. Combining an ACT with an endectocide treatment that is able to reduce vector survival, such as ivermectin (IVM), could increase the impact of MDA and offer a new tool to reduce malaria transmission.

**Objective:**

The study objective is to evaluate the impact of MDA with IVM plus dihydroartemisinin-piperaquine (DP) on malaria transmission in an area with high coverage of malaria control interventions.

**Methods:**

The study is a cluster randomized trial in the Upper River Region of The Gambia and included 32 villages (16 control and 16 intervention). A buffer zone of ~2 km was created around all intervention clusters. MDA with IVM plus DP was implemented in all intervention villages and the buffer zones; control villages received standard malaria interventions according to the Gambian National Malaria Control Program plans.

**Results:**

The MDA campaigns were carried out from August to October 2018 for the first year and from July to September 2019 for the second year. Statistical analysis will commence once the database is completed, cleaned, and locked.

**Conclusions:**

This is the first cluster randomized clinical trial of MDA with IVM plus DP. The results will provide evidence on the impact of MDA with IVM plus DP on malaria transmission.

**Trial Registration:**

ClinicalTrials.gov NCT03576313; https://clinicaltrials.gov/ct2/show/NCT03576313

**International Registered Report Identifier (IRRID):**

DERR1-10.2196/20904

## Introduction

Between 2000 and 2015, the burden of malaria decreased substantially in sub-Saharan Africa following the scale-up of insecticide-treated bed nets (ITNs), indoor residual spraying (IRS), and artemisinin-based combination therapy [1,2]. In The Gambia, between 2003 and 2007, the proportion of blood slides positive for malaria decreased by 74%, and hospital admissions for malaria by 81% [3,4]. Nevertheless, despite the high coverage of control interventions, malaria transmission has become increasingly heterogeneous [5-7]. Innovative interventions and tools to further reduce transmission and eliminate malaria are needed.

Mass drug administration (MDA), a full antimalarial treatment to all inhabitants of target communities regardless of their infection status, has been identified as a potential tool to further reduce transmission where coverage of vector control interventions is already high [8,9]. MDA with artemisinin-based combination therapy (ACT) reduces transmission by clearing asexual infections and early-stage gametocytes in asymptomatic, infected individuals [8,9]. Dihydroartemisinin-piperaquine (DP), thanks to its simple dosing schedule, long posttreatment prophylaxis period, good safety profile [10,11], and the fact that it is not used as a first-line antimalarial treatment in The Gambia, is a promising candidate for MDA. However, the effect of MDA with ACT on malaria is limited over time [12,13]. This limited impact is largely attributed to incomplete coverage and the persistence of malaria parasites in the mosquito population, with a smaller contribution to residual transmission of gametocytes remaining after ACT administration [14].

Combining an antimalarial treatment (DP) with an endectocide treatment able to reduce vector survival, ivermectin (IVM), could increase the impact of MDA and offer a new tool to reduce malaria transmission [15,16]. IVM is a broad-spectrum antiparasitic endectocidal drug, active against a wide range of parasites, including ectoparasites [17]. It reduces the lifespan of mosquitoes that feed on treated individuals [16], with conflicting data on a possible effect on parasite development in surviving mosquitoes [18-20]. A major advantage of IVM is that, since malaria vectors feed on more than one person, the effective coverage may exceed MDA coverage, especially if its mosquitocidal effect can be extended by repeated treatments. Repeated IVM dosing increases the duration of time that IVM concentration remains above the lethal concentration that kills 50% of mosquitoes [17]. A 3-day regimen of IVM 300 µg/kg is safe and has a mosquitocidal effect for *Anopheles gambiae s.s*. lasting approximately 28 days post treatment [16].

The community administration of IVM could reduce malaria transmission [19,21], providing a synergistic effect compared to MDA with ACTs alone [15]. Furthermore, IVM can reduce the prevalence of other parasitic infections, including ectoparasites and soil-transmitted helminths, which could be an important additional benefit and improve the cost-effectiveness of this intervention.

The mass drug administration of ivermectin and dihydroartemisinin-piperaquine as an additional intervention for malaria elimination (MASSIV) study is a cluster randomized trial that aims to evaluate the impact of MDA with IVM plus DP on malaria transmission in an area with high coverage of malaria control interventions, eg, ITNs, IRS, and seasonal chemoprevention (SMC). The trial was implemented in Basse, Upper River Region (URR) in The Gambia.

### Study Objectives

#### Clinical

The clinical objective is to determine whether three monthly rounds of MDA with IVM plus DP implemented over two malaria transmission seasons will reduce malaria transmission in communities with high coverage of malaria control interventions.

#### Entomological

The entomological aim is to determine whether three monthly rounds of MDA with IVM plus DP implemented over two malaria transmission seasons will reduce vector parity, a proxy for vector survival, in communities with high coverage of malaria control interventions.

#### Social Science and Health Economics

The social science and health economics aims are to (1) identify the most socially acceptable and sustainable way of achieving and maintaining high coverage of MDA with IVM plus DP, and (2) determine the costs and cost-effectiveness of this intervention compared to standard malaria control measures.

## Methods

### Study Design

The study is a cluster randomized trial (ClinicalTrials.gov, NCT03576313) that included a total of 32 villages (16 control and 16 intervention), located at least 3 km from each other. A buffer zone of ~2 km was created around all intervention clusters in a modified fried-egg design [22]. No buffer zone was created around control villages. MDA with IVM plus DP was implemented in all intervention villages and the buffer zones; control villages received standard malaria interventions according to the Gambian National Malaria Control Program’s (NMCP) plans.

### Study Setting

The study was conducted in the eastern part of The Gambia in the Upper River Region (URR). The region is open Sudanese savanna and covers an area of 1995 km^2^ [23]. Most of the residents are subsistence farmers. The climate is characterized by a long dry season from mid-October to mid-June, followed by a single short rainy season. Malaria transmission is highly seasonal, with most malaria cases occurring during the rainy season and immediately afterward, until December-January [23,24]. Malaria transmission has decreased substantially in The Gambia; however, it is higher in URR than in other regions [24]. The URR is also characterized by low vector density and high vector parity rate, indicating high vector survival, suggesting the existence of populations (or subpopulations) of mosquitoes able to escape standard vector control interventions [24].

### Selection of Villages and Informed Consent

A cross-sectional survey was carried out in November 2017, at the peak of malaria transmission, in 47 medium-sized (200-600 inhabitants) villages to select study villages with a baseline malaria prevalence of at least 10%. Following the survey, 32 villages with malaria prevalence determined by qPCR of at least 10% were included in the trial and randomly assigned to either the intervention or control arm using STATA, version 15; randomization was constrained such that the mean baseline prevalence in the intervention clusters was within ±10% of the prevalence in the control clusters.

After explaining the study objective and methods of the trial to the local authorities and the populations of the study villages through sensitization meetings in the local language, a census of the study population was carried out in November 2017. This was followed by individual consent procedures to obtain written informed consent for all willing residents in the study villages. Consent for children was provided by their parents/guardians; assent was sought for adolescents 12-17 years old.

Consent and enrolment procedures were carried out throughout the trial to obtain written informed consent from new residents and individuals missed previously by the research team due to absence at the time of the initial consenting and enrolment procedures.

A list of all residents in the study villages, by compound, including consent status, were generated and made available to the study team.

### Eligibility Criteria

The target population for MDA was all eligible individual residents in the intervention villages. During each MDA round, residents were (re)assessed for eligibility to receive IVM and DP. Participants had to meet all inclusion criteria and none of the exclusion criteria. Inclusion criteria were: (1) age/anthropometry, for IVM: weight ≥15 kg; for DP: age >6 months, (2) willingness to comply with trial procedures, and (3) individual written informed consent. The exclusion criteria for both IVM and DP were known chronic illnesses such as HIV, tuberculosis, hepatitis, and severe malnutrition. Additionally, for IVM only, exclusion criteria were (1) pregnancy (any trimester) or breastfeeding, (2) hypersensitivity to IVM, and (3) travel to *Loa loa* endemic countries (Central Africa); for DP, these were: (1) first-trimester pregnancy, (2) hypersensitivity to DP, and (3) taking drugs that influence cardiac function or prolong QTc interval.

### Trial Medication and Intervention

DP (Guilin Pharmaceuticals, China) was available as tablets of 320/40 mg and 160/20 mg piperaquine/dihydroartemisinin per tablet. DP was administered orally, once daily for three days, according to body weight per manufacturer’s guidelines. For participants unable to swallow the tablets, such as infants and young children, DP was crushed and mixed with water. The mixture was used immediately after preparation. If a participant vomited within 30 minutes of taking DP, the full dose was readministered; if a patient vomited within 30-60 minutes, half the dose was readministered. IVM (Laboratorio Elea SACIF y A, Argentina) was available as 6 mg tablets. It was given at 300-400 μg/kg/day once daily for three days (15.0-25.9 kg one tablet, 26.0-40.9 kg two tablets, 41.0-60.9 kg 3 tablets, 61.0-80.9 kg four tablets, 81.0-95.9 kg five tablets, ≥96 kg 6 tablets). Therefore, the total dose of IVM for each round was 900-1200 μg/kg. Before treatment, women of reproductive age (15-49 years) were asked to provide a urine sample to test for pregnancy. All treatments were supervised.

MDA was implemented each year and for two consecutive transmission seasons as three-monthly rounds starting from July (end of the dry season) to August and September (rainy season). The choice of implementing the intervention for two consecutive years was taken to estimate its cumulative effect and to monitor community participation over repeated intervention rounds.

Standard malaria control interventions were implemented in both intervention and control villages. These consisted of ITNs, IRS with pirimiphos-methyl (Actellic 300CS) done in mid-July 2019, just before the first MDA round of IVM and DP, prompt diagnosis and treatment with artemether-lumefantrine, SMC, and intermittent preventive treatment during pregnancy (IPTp). During the three rounds of MDA, SMC was not administered to children in the intervention villages eligible for MDA with IVM plus DP to avoid double antimalarial treatment. In these villages and during the MDA period, only children aged 3-6 months received SMC as they were not eligible for DP treatment. Nevertheless, all children aged 3-59 months received SMC one month after completing the last MDA round in intervention villages. The implementation of these malaria control interventions was done by the Regional Health Team and documented at the level of individual participants. Eligible children in control villages received SMC as planned by the NMCP.

### Outcome Measures

#### Clinical

The primary clinical endpoint was the prevalence of malaria infection measured by qPCR in all age groups [25] via a yearly cross-sectional survey at the peak of the transmission season in November.

Secondary endpoints included (1) incidence of clinical malaria estimated by passive case detection by recording all clinical cases from study villages (both intervention and control) attending the local health facilities or the community health worker when present; (2) prevalence of drug-resistant markers such as Pfcrt and Pfmdr-1 mutations [26], in malaria-positive blood samples collected during the annual cross-sectional survey; (3) serological markers of recent malaria infection and recent Anopheles exposure, both determined by detecting relevant antibody responses in blood samples collected during the annual cross-sectional survey; (4) intervention coverage as the proportion of eligible individuals having taken the investigational products.

Tertiary endpoints were the prevalence of bedbugs, headlice, scabies, and soil-transmitted helminths. Surveys were done yearly, before and after the MDA campaign.

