### Randomization and Blinding

The unit of randomization was the village. Randomization to the intervention or the control arm was done by computer-based randomization. To prevent imbalance for potential confounding factors, restricted randomization to balance the arms on factors such as baseline prevalence, ITN coverage, and distance from health facilities was used [22].

Considering the nature of the trial (cluster randomized), the primary endpoint (malaria prevalence), and the logistical and ethical (treating thousands of individuals with placebo) challenges, we chose not to blind participating individuals. All laboratory staff involved in processing samples and evaluations contributing to any clinical or entomological endpoints were blinded to the allocation arm.

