### Study Procedures and Evaluations

#### Clinical Evaluation

Passive case detection was established at local health facilities and the village level if community health workers were present. All suspected malaria cases, such as patients with fever or history of fever in the last 24 h without any other apparent illness, were investigated with an RDT (SD BIOLINE Malaria Ag Pf Standard Diagnostics); if positive, the patient was treated with artemether-lumefantrine, the first-line treatment in The Gambia. Axillary body temperature was measured using an electronic thermometer; a blood slide and blood spots were collected for later molecular analysis. Randomly selected individuals, regardless of temperature or history of symptoms, were included in the cross-sectional surveys to collect blood samples by finger prick and administer a short questionnaire on demographic characteristics, area of residence, recent travel history, and use of malaria control interventions and recent history of clinical malaria.

A cross-sectional survey to estimate the prevalence of ectoparasites, scabies, and helminths was carried out. In each cluster, 30 children aged 4-13 years, the age group at highest risk of these infections, were selected. Bedbugs were detected by visual inspection of the child’s bed using torchlight, and headlice were detected by visual search of the scalp. Scabies was identified by a complete physical examination of the body. A stool sample was taken to identify the presence of helminths, including *Strongyloides stercoralis, Trichuris trichiura*, *Necator americanus*, *Ancylostoma duodenale*, and *Ascaris lumbricoides* using PCR.

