### Statistical Analysis

The primary clinical endpoint, malaria prevalence at the end of the second transmission season, will be compared between arms using random**-**effects logistic regression, and a random effect for study village will be included to account for clustering. An odds ratio, 95% CI, and *P* value will be presented. Malaria prevalence at the end of the first transmission season will be analyzed separately and in the same way.

The primary entomological endpoint, vector parity, will be compared between arms using random-effects logistic regression, and a random effect for study village will be included to account for clustering. A fixed effect for study month and year will be included. An odds ratio, 95% CI, and *P* value will be presented. Incidence will be compared between arms using random-effects Poisson regression, and a random effect for study village will be included to account for clustering. An offset for village population and a fixed effect for the study year will be included. A rate ratio, 95% CI, and *P* value will be presented. Mosquito mortality, a secondary entomological endpoint, will be determined by Kaplan-Meier estimates. Kaplan-Meier plots of mosquito survival will be presented for each age group and timepoint. A comparison between the arms will be made using survival analysis with an exponential survival model. A random effect (shared frailty) will be included for each human participant to account for correlated outcomes on mosquitoes fed on the same participant.

Other entomological endpoints: (1) Mosquito density will be compared between arms using random**-**effects negative binomial regression, and a random effect for study village will be included to account for clustering. A fixed effect for study month and year will be included. An odds ratio, 95% CI, and *P* value will be presented; (2) Sporozoite rates in field-caught mosquitoes will be compared between arms using random**-**effects logistic regression, and a random effect for study village will be included to account for clustering. A fixed effect for study month and year will be included. An odds ratio, 95% CI, and *P* value will be presented.

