### Quality Management

An independent data and safety monitoring board (DSMB) was appointed to advise the sponsor and investigators on the trial’s safety issues. Study physicians and nurses were trained to monitor and report all adverse events, including serious adverse events associated with treatment. Before each dose, adverse events that occurred were systematically documented by medical terms, start and end date, severity and seriousness, relation to the study drug, and outcome. The relationship to the study drugs was determined based on temporal association and clinical judgment. The study nurses visited each household in intervention villages 7 days after starting treatment to monitor and document any adverse events in the study population. Serious adverse events were reported to the DSMB, the local ethics committee, and the London School of Hygiene and Tropical Medicine (LSHTM) Ethics Committee. Analysis of adverse events was restricted to the intervention arm because the study population in the control arm was not treated with the investigational products.

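### The incidence model has no fixed effect for community health worker presence, which decides how cases are found in a village: this costs precision and leaves chance imbalance, but does not bias the rate ratio

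*Protocol article*

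**What the plan says.** **Case capture.** Outcome Measures (Clinical) lists incidence first among the secondary endpoints and counts it passively, by "recording all clinical cases from study villages (both intervention and control) attending the local health facilities or the community health worker when present". Clinical Evaluation repeats the condition: "Passive case detection was established at local health facilities and the village level if community health workers were present". The number of villages with a worker is not given.

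**Model.** Statistical Analysis specifies random-effects Poisson regression with a random effect for village. Its remaining terms are: "An offset for village population and a fixed effect for the study year will be included".

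**Allocation.** Randomization and Blinding names baseline prevalence, ITN coverage and distance from health facilities as balance factors. The list is given as examples. Worker presence is not on it.

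**Contact by arm.** Quality Management says that adverse events were documented before each dose, and: "The study nurses visited each household in intervention villages 7 days after starting treatment to monitor and document any adverse events". No matching contact is described for control villages.

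**The concern.** Two features affect how many true cases reach the count.

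The first is a village characteristic. Where a worker is present, a person with fever can be tested in the village; elsewhere only those who travel to a facility are counted. If this changes detection, observed rates will differ between villages for a reason unrelated to transmission. That widens the interval around the rate ratio, and any uneven split of worker villages between the arms shifts the estimate. The characteristic is a plain village-level fact, so it could be adjusted for.

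The second follows the arm. Three supervised daily doses and a day-7 household visit in each of three rounds make (3 + 1) × 3 = 12 contacts per season for someone treated in every round. Illness mentioned at such a contact might be sent on to a facility and enter the count, or be dealt with on the spot and never enter it. The article does not say which, and the contacts exist in one arm only.

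The rate ratio for clinical malaria is at stake. The primary endpoint, qPCR prevalence by survey in both arms, is not affected.

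**Working it through.** **Inputs from the protocol article:** 16 villages per arm; prevalence 15% versus 7.5%; coefficient of variation 0.5; 200 people per cluster; 90% power. There is no sample size or power for incidence, and there are no detection rates.

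**Assumptions:** 16 of 32 villages have a worker (8 and 24 also tried); a worker multiplies detected cases by r = 1.5 or 2; other between-village variation in incidence has a coefficient of variation of 0.5, borrowed from the prevalence calculation; two-sided alpha 0.05.

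**1. The plan's own figure.** The 0.5 is the value behind the prevalence sample size, which reproduces:

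c = 1 + (1.96 + 1.282)² × [0.15×0.85/200 + 0.075×0.925/200 + 0.5²×(0.15² + 0.075²)] / 0.075² = 1 + 14.97 = 15.97, so 16 clusters per arm. Power with 16 is 90.05%, against the stated 90%.

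**2. Precision.** With half the villages having a worker, the between-village variance of the log rate due to workers is (ln r / 2)²: 0.041 for r = 1.5 and 0.120 for r = 2. Other variance is ln(1 + 0.5²) = 0.223. Worker presence then explains

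- r = 1.5: 0.041 / 0.264 = 16%
- r = 2: 0.120 / 0.343 = 35%

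Removing that share would shorten the confidence interval on the log scale by up to 1 − √0.84 = 8% or 1 − √0.65 = 19%. These are upper limits, because Poisson variation within villages is ignored.

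**3. Chance imbalance.** If X of the 16 worker villages fall in the intervention arm, the rate ratio is multiplied by r^((2X − 16)/16).

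- A 10:6 split gives r^0.25 = 1.11 (r = 1.5) or 1.19 (r = 2). Under unrestricted allocation X is hypergeometric, and a split of 10:6 or worse, in either direction, has probability of about 29%.
- The 2.5% and 97.5% points fall at splits of 5:11 and 11:5, that is r^(±0.375): 0.86 to 1.16 (r = 1.5) or 0.77 to 1.30 (r = 2).
- With 8 or 24 worker villages the ranges are 0.90 to 1.11 and 0.84 to 1.19.

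**4. Bias and type I error.** Over 40,000 random allocations the mean shift in the log rate ratio was about zero in every scenario (largest 0.0011 in absolute value). In simulations under no effect (400 people per village, 0.1 cases per person, SD of log rate 0.47, and a t-test on village log rates standing in for the Poisson model), the rejection rate with worker presence left out was 0.0505 (r = 1.5) and 0.0487 (r = 2).

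**5. Detection differing by arm.** Observed rate ratio = true rate ratio × (detection in intervention / detection in control). For an assumed detection ratio of 0.8 or 1.2:

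| True rate ratio | Ratio 0.8 | Ratio 1.2 |
|---|---|---|
| 1.0 | 0.80 | 1.20 |
| 0.5 | 0.40 | 0.60 |

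In the same simulation the rejection rate under no effect rose to 0.17–0.23 (ratio 0.8) and 0.12–0.17 (ratio 1.2). The contacts occur in all intervention villages and in no control village, so a model term for them would be the arm indicator itself.

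**The case against.** The case against is substantial, and most of it stands.

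- A reader might infer that the model ignores detection differences between villages and that the rate ratio is therefore biased. It does not ignore them: the village random effect takes them up and the standard error reflects them. With randomized villages the 10:6 figures are chance imbalance, not bias. Restriction on distance from facilities may also limit the imbalance.
- A reader might infer that the nurse visits distort the incidence comparison. The documents do not show this. The endpoint is already limited to people attending a facility or worker, and the visits are described as adverse event monitoring. They also fall just after a full antimalarial course with a long prophylactic period, when little malaria should surface. Twelve contacts is a maximum; the sample size section assumes 63% receive three courses.
- A reader might add that unblinded staff decide who is tested. The article says "we chose not to blind participating individuals" and that laboratory staff were blinded; it does not state the position of facility staff or community health workers. Blinded reading of stored specimens would not undo that first clinical judgement, since specimens come from suspected cases who have already passed it.
- Precision covariates for a secondary endpoint are often left to the SAP. True, and the SAP is not shown. The article does, however, state the terms of this model, so the point is an improvement to a stated specification and not a complaint of omission.

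What remains is a known village-level source of variation that could be adjusted for, and a one-arm contact whose effect on the count cannot be checked from the analysis described.

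**Conclusion.** The point holds in a limited form. Case capture for the incidence endpoint depends on whether a village has a community health worker, and the stated model has no fixed effect for this. The consequence is lost precision and unadjusted chance imbalance, with no expected bias and type I error near 5%. Over the assumed range (workers in half of the villages, detection raised 1.5- to 2-fold, unrestricted allocation) chance imbalance can move the rate ratio over 0.86 to 1.16 up to 0.77 to 1.30. It is less if fewer or more villages have a worker, and nothing if workers do not change detection.

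The arm-level contact is a risk of unknown size and direction, not a demonstrated distortion. The 0.8 and 1.2 detection ratios only illustrate how directly such a difference would pass into the rate ratio. Both parts concern a secondary endpoint.

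**What to change.** 1. Add a village-level fixed effect, community health worker present at baseline (yes/no), to the random-effects Poisson model. Baseline status is used so that the covariate cannot be affected by the intervention. The cost is one between-village degree of freedom out of 32 villages (30 to 29 for a two-arm comparison) and one item of village data.

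2. Keep the passive count as defined under Outcome Measures for the main incidence analysis. Add one sensitivity analysis that omits the same dosing and day-7 calendar windows from both arms. This needs case dates only and loses the cases in those windows. It shows whether the result depends on the contact periods, but it cannot detect an effect of the contacts that persists beyond them.

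3. Do not drop cases first identified at study visits from the intervention arm alone. That would remove true cases from one arm, including people who would have attended anyway, and would push the rate ratio towards benefit.

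The article says analysis will begin only after database lock, so both additions can still be specified in advance.
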